### Sample size estimation

Sample size estimation is performed using PASS software (v15.0) with reference to prior studies (42, 43). Assuming an effect size of 0.5 for WAB-AQ, a sample size of 16 per group would provide 80% power at a two-sided significance level of 0.05. To account for an anticipated 20% dropout rate, we plan to enroll 20 participants in each group.

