## Introduction

Post-stroke aphasia (PSA) affects around 30% of stroke survivors and is frequently associated with enduring language impairments that significantly diminish quality of life and elevate healthcare burdens (1). These deficits spanning spontaneous speech, comprehension, repetition, and naming, not only hinder daily communication but also impair rehabilitation progress and long-term outcomes (2, 3). Speech and language therapy (SLT) remains the standard intervention for PSA, its benefits are often modest (SMD = 0.28) (1). Noninvasive brain stimulation techniques, particularly repetitive transcranial magnetic stimulation (rTMS), emerge as promising adjuncts for enhancing language recovery in PSA (2, 4, 5). The intermittent theta burst stimulation (iTBS), a specific rTMS protocol, offers unique advantages through its ability to induce an increase in cortical excitability with shorter treatment durations (6, 7).

Optimizing stimulation targets is critical for maximizing the therapeutic benefits of rTMS. Although traditional approaches have focused on perisylvian language—related areas, including inferior frontal gyrus (IFG) and superior temporal gyrus (STG) (8, 9), growing evidence highlights the importance of domain-general networks involving aphasia recovery (10, 11). Such domain-general regions underpin various cognitive processes, including working memory, reasoning, attention, and executive function (12). The cingulo-opercular network, a key domain-general network consisting of the dorsal anterior cingulate cortex, pre-supplementary motor area (pre-SMA), anterior insula, and inferior frontal gyrus, is implicated in post-stroke language recovery (12–14).

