### Randomization

Participants will be randomly allocated in a 1:1 ratio to either the active iTBS or sham group. Randomization will be stratified by aphasia subtype (non-fluent only) to maintain balanced group allocation. The allocation sequence will be safeguarded through the use of consecutively numbered, sealed opaque envelopes, which are prepared and kept by personnel independent of the trial. Prior to the intervention, an independent researcher (not blinded) will open the corresponding envelope to determine and confirm each participant's group allocation.

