## Data analysis

### Behavioral data

Repeated-measures ANOVAs are used to assess changes in WAB, BNT, NLCA scores, and speech parameters, with phase (pre- vs. post-treatment) as a within-subject factor and group (active vs. sham iTBS) as a between-subject factor. *Post hoc* comparisons are adjusted using the Bonferroni method. Data normality is checked with the Kolmogorov–Smirnov test; non-normally distributed variables are analyzed using the Wilcoxon signed-rank test. An intention-to-treat (ITT) approach is applied in the presence of missing data.

In cases where the assumptions of normality or homogeneity of variances are violated, a non-parametric Aligned Rank Transform (ART) ANOVA was applied to test for main and interaction effects. This approach preserves the interpretability of ANOVA-type models while providing robustness to deviations from normality. For *post-hoc* comparisons, the Wilcoxon signed-rank test (within-group) and Mann–Whitney *U*-test (between-group) are used with Bonferroni correction.

To further explore variability in treatment response, a sub-analysis will be performed within the non-fluent aphasia cohort, stratifying participants according to their baseline WAB-AQ scores to examine severity-related differences in iTBS efficacy. Participants will be categorized into mild (WAB-AQ: 50.4–93.7), moderate (30.1–50.3), and severe (0–30) aphasia groups based on their baseline scores (55). Changes in primary behavioral outcomes (WAB, BNT, NLCA) will be compared across these severity strata using mixed-design ANOVAs, followed by Bonferroni-corrected *post hoc* tests. This analysis aims to explore potential differential treatment responses across varying degrees of language impairment.

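### The stated 80% power for an effect size of 0.5 with 16 per group is wrong: a two-arm comparison of that size has about 28% power

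*Protocol article*

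**What the plan says.** The section on sample size estimation in the protocol article sets out a complete power statement for the primary outcome: "Assuming an effect size of 0.5 for WAB-AQ, a sample size of 16 per group would provide 80% power". The test level is 5%, two-sided. The section credits PASS v15.0 and prior studies, and raises 16 to 20 per group for 20% dropout. It does not say which effect-size metric the 0.5 is, and it gives no SD, no difference in AQ points, no correlation between visits and no test.

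The design is a two-arm comparison: "Participants will be randomly allocated in a 1:1 ratio to either the active iTBS or sham group" (Randomization). The behavioural analysis is a repeated-measures ANOVA "with phase (pre- vs. post-treatment) as a within-subject factor and group (active vs. sham iTBS) as a between-subject factor". Where the Introduction puts a size on a treatment benefit, that of speech and language therapy (SLT), it uses a standardised mean difference of 0.28.

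**The concern.** An unqualified effect size of 0.5 on a continuous score in a two-arm trial is ordinarily a standardised mean difference, and that is the metric the article uses elsewhere. On that reading a difference of half an SD needs about four times the stated number per arm, so the four printed figures (0.5, 16 per group, 5% two-sided, 80%) do not fit together.

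This paragraph is the only justification for the sample size. Readers and the ethics committee are told the trial has a four-in-five chance of detecting its planning effect, when the chance is nearer one in four. A non-significant result could then be taken as evidence against pre-SMA stimulation, although the trial had little chance of finding the effect it planned for.

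**Working it through.** **Inputs.** Effect size 0.5, 16 per group before dropout, two-sided 5%, 20% dropout (Sample size estimation); 1:1 allocation (Randomization); group by phase ANOVA with two phases (Behavioral data).

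**1. The plan's own figure, 0.5 read as a standardised difference d.** For a two-sample t-test the noncentrality is d × √(n/2) with 2n − 2 degrees of freedom.
- n = 16: 0.5 × √8 = 1.414, 30 df, two-sided critical value 2.042. Power = **27.8%** (29.3% by normal approximation). The stated 80% is not reproduced.
- n = 20, no dropout: power = **33.8%**.

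**2. Number needed for 80% at d = 0.5.** Normal approximation: 2 × (1.96 + 0.84)² / 0.5² = 62.8, so 63 per group. The exact t-test gives 79.5% at 63 and 80.1% at **64 per group**.

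**3. Effect detectable with 80% power at 16 per group.** Solving the t-test power for d gives **1.02 SD** (0.99 by normal approximation). As a sense of scale only, 1.02 / 0.28 ≈ 3.6 times the SLT benefit quoted in the Introduction.

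**4. Dropout step.** 16 / (1 − 0.2) = 20. This is correct.

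**5. Does another reading give 80% at 16 per group?** With two phases, the group by phase interaction is the same test as comparing mean change between arms. If 0.5 is in units of the raw-score SD and r is the correlation between visits, the effect on the change scale is 0.5 / √(2(1 − r)). For ANCOVA it is 0.5 / √(1 − r²).

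| Reading (16 per group) | Power | Unstated input or mismatch |
|---|---|---|
| One-sided 5% | 39.6% | Section says two-sided |
| Paired test within one arm of 16 | 46.5% | Does not compare arms |
| Change score, r = 0.5 | 27.8% | r |
| Change score, r = 0.7 | 42.4% | r |
| Change score, r = 0.8 | 58.1% | r |
| Change score, r ≈ 0.88 | 80% | r |
| ANCOVA, r = 0.7 / 0.8 | 48.3% / 62.6% | r; ANCOVA is not the ANOVA described |
| ANCOVA, r ≈ 0.87 | 80% | r; ANCOVA is not the ANOVA described |
| Cohen's f = 0.5, one-way | 78.1% (80.7% by normal approximation) | f = 0.5 is d = 1.0 |
| Interaction, f = 0.25, r = 0.5 | 78.1% | Metric and r; a 1.0 SD difference in change |
| Interaction, f = 0.5, r = 0 / 0.5 | 97.2% / 99.98% | Metric and r; overshoots 80% |
| Group effect averaged over two visits, f = 0.5, r = 0.5 / 0.8 | 88.5% / 82.2% | Metric and r; not the treatment contrast |

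**6. A possible origin.** A one-sample or paired test at 0.5 needs (1.96 + 0.84)² / 0.25 = 31.4 participants by normal approximation, close to 32 = 2 × 16, so a total for the wrong test may have been split over two arms. This is conjecture: the exact t-test needs 34 (78.2% at 32), and the f readings fit about as well. Nothing below depends on it.

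**The case against.** The strongest reply is that the section never names the metric, and that the planned test is an ANOVA, where effect size is often given as Cohen's f. With f = 0.5, 16 per group gives 78% exactly and just over 80% by normal approximation. With f = 0.25 on the interaction and a correlation of 0.5 it also gives 78%. On this view the effect size is mislabelled rather than the power miscalculated.

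That stands as far as it goes, and the sponsor should be asked which was meant. It does not rescue the paragraph. Each of these f readings corresponds to a between-arm difference of about 1 SD, twice what a reader takes 0.5 to mean. The only route that keeps 0.5 as a standardised difference needs a correlation near 0.88 (0.87 with ANCOVA), which is possible but not stated.

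Three smaller points also have some force. The 0.28 is the benefit of SLT, which both arms receive, so it is only a yardstick and not an expected iTBS effect. The article contains no rule that treats a null result as evidence of no effect, and its Limitation section says that small samples in many studies compromise power; it does not, however, correct or qualify the 80%. Finally, restating the detectable effect leaves the trial underpowered for 0.5 SD, so a sponsor who needs that effect would have to revisit the sample size.

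**Conclusion.** The power statement is wrong as printed. With 0.5 as a standardised mean difference, a two-arm comparison at two-sided 5% has 27.8% power with 16 per group, about 52 percentage points below the stated 80%, and 33.8% with all 20 per group. The design has 80% power only for about 1.02 SD.

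This rests on the ordinary reading of effect size and on no unstated gain from baseline correlation. If 0.5 was Cohen's f, the power is about right (78%) but the trial is powered for 1.0 SD and the effect is mislabelled. If a correlation of about 0.88 was assumed, 80% is attainable but the assumption is missing. The paragraph needs correcting in every case.

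**What to change.** Restate the sample size paragraph before results are known:

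- With 16 evaluable per group, the trial has 80% power for a between-arm difference of 1.02 SD in WAB-AQ and about 28% power for 0.5 SD.
- If 0.5 was Cohen's f, or the calculation relied on a correlation of about 0.88 between baseline and post-treatment scores, say so. Give the test, the SD, the correlation and its source, and the difference in AQ points, and correct the power to match.
- State that the treatment effect will be reported as an estimate with a 95% confidence interval, and that a non-significant result will not be read as showing no effect.

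The cost is one reworded paragraph and a less favourable stated power. Enrolment need not change. For reference, keeping 80% power for a 0.5 SD difference without a stated correlation would take 64 evaluable per group, or 64 / 0.8 = 80 enrolled per group and 160 in total.

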### Randomization

Participants will be randomly allocated in a 1:1 ratio to either the active iTBS or sham group. Randomization will be stratified by aphasia subtype (non-fluent only) to maintain balanced group allocation. The allocation sequence will be safeguarded through the use of consecutively numbered, sealed opaque envelopes, which are prepared and kept by personnel independent of the trial. Prior to the intervention, an independent researcher (not blinded) will open the corresponding envelope to determine and confirm each participant's group allocation.

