Our personalized targeting strategy aligns with the bimodal balance–recovery model of post-stroke rehabilitation (38). This framework proposes that functional recovery mechanisms are determined by the degree of structural reserve in the damaged hemisphere. When substantial white matter integrity is preserved (high structural reserve), recovery primarily occurs through remodeling of ipsilesional networks (interhemispheric competition model). Conversely, when structural damage is severe (low structural reserve), compensation predominantly relies on contralesional hemisphere recruitment (compensatory model). To operationalize this model clinically, we employ DTI to quantify the structural integrity of the left frontal aslant tract (FAT), thereby guiding individualized decisions to target either the ipsilesional or contralesional pre-SMA. Moreover, this trial specifically focuses on the early subacute phase (1–3 months post-stroke), which is recognized as a critical window for neuroplasticity and recovery. During this period, beneficial disinhibition and reorganization processes occur within motor and language networks, facilitating experience-dependent cortical remapping and responsiveness to neuromodulation (39–41). Selecting this time window is therefore intended to maximize the potential efficacy of individualized pre-SMA stimulation.

The current study has two primary objectives: (1) to determine whether fMRI-guided, individualized pre-SMA iTBS enhances language recovery in subacute PSA compared to sham stimulation, and (2) to characterize the neuroplastic mechanisms of treatment effects by examining pre-SMA-related circuit reorganization and functional connectivity changes within language network and domain-general cognitive networks. Our findings may establish a new precision medicine paradigm for aphasia rehabilitation that integrates connectivity-based targeting with biologically informed treatment protocols.

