**Figure 1 F1:**
[figure not shown]
Study design and data collection.

**Table 1 T1:** Timeline of enrolment and assessments.

**Time-point**	**Screening and allocation**	**Post-randomization**		**Follow-up**
	**Day** −**7**~−**1**	**Day 0**	**Day 14 (**±**3 day)**	**Day 44 (**±**3 day)**

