### Participants and recruitment

Participants will be recruited from Wuxi Central Rehabilitation Hospital. Eligibility requires meeting all of the following items: (1) a confirmed diagnosis of aphasia secondary to ischaemic stroke, with symptoms lasting between 1 and 3 months; (2) left-hemisphere ischaemic stroke confirmed by brain CT or MRI scan; (3) a first-ever stroke with a single lesion; (4) Aphasia Quotient (AQ) on the WAB < 93.8; (5) aged between 50 and 75 years; (6) native Mandarin speakers with at least primary school education; (7) right-handedness; (8) intact premorbid language function; (9) informed about the procedures of iTBS treatment and brain imaging scans, and provided written informed consent.

Given the focus of the current protocol, only patients with non-fluent aphasia (as classified by the WAB) will be included. The aphasia type of all enrolled participants will be determined and documented at baseline to ensure diagnostic accuracy and sample homogeneity.

Exclusion criteria include: (1) severe auditory, visual, or cognitive deficits limiting compliance; (2) significant dysarthria (NIHSS item 10 ≥ 2); (3) impaired consciousness (NIHSS item 1a ≥ 1); (4) major psychiatric disorders such as severe depression or anxiety that may interfere with participation; (5) aphasia due to other causes (e.g., brain tumor, traumatic brain injury, Parkinson's disease, motor neuron disease); (6) history of epilepsy or substance abuse; (7) contraindications to TMS or fMRI (e.g., scalp lesions, defects of the skull, intracranial implants, pacemakers, or drug pumps).

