### Blinding

This trial adopts a double-blind design to ensure that both participants and key study personnel remain unaware of treatment allocation. Blinding extends to participants, family members, caregivers, treating physicians, TMS operators, outcome assessors, and data analysts. Blinding procedures are outlined in the informed consent, and treatment schedules and follow-up visits are arranged to minimize potential interactions among participants.

Active and sham stimulation are delivered using a figure-of-eight double-sided coil, which has an active side for real stimulation and a placebo side that mimics the auditory and somatosensory sensations without generating an effective magnetic field. For sham stimulation, the coil is flipped, positioning the placebo side toward the scalp while maintaining an identical appearance to the active condition. To ensure full blinding, the resting motor threshold (RMT) assessment and iTBS intervention are performed by different personnel. A designated unblinded technician conducts the RMT measurement using the active side of the coil and records the motor threshold value. To preserve allocation concealment, unblinded staff label coils as “A” or “B” and perform randomization once individualized iTBS targets are determined. Only these personnel are aware of the actual mapping between labels and stimulation type. During the intervention, TMS operators are informed only which side (“A” or “B”) of the coil to use, without knowledge of the stimulation type. Imaging data are processed by blinded analysts, ensuring that group allocation remains undisclosed throughout the study.

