**Figure 2 F2:**
[figure not shown]
Personalised stimulation target localisation protocol. This figure illustrates the process of localising personalised TMS targets for language rehabilitation.

The FAT's fractional anisotropy (FA) will evaluate bilaterally. The FA ratio between the affected and unaffected sides was defined as relative FA (rFA, rFA = FAipsilesional/FAcontralesional), following the method used to evaluate the corticobulbar tract (CBT) in stroke recovery (45). As defined in prior studies, an rFA > 0.5 indicates high integrity, while an rFA ≤ 0.5 indicates low integrity. It should be noted that the specific rFA threshold for defining a functionally intact FAT has not been established in the literature. Therefore, we have extrapolated from studies on other major tracts, such as the corticospinal tract (CST) and CBT, in which an rFA > 0.5 correlates with preserved motor and swallowing function (45–47). Participants with high FAT integrity receive stimulation over the ipsilesional pre-SMA, while those with disrupted FATs are stimulated over the contralesional pre-SMA.

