## Limitation

The current study presents several limitations that warrant consideration. First, the recruitment of participants with PSA remains challenging, resulting in relatively small sample sizes in many studies. This limitation compromises statistical power and consequently restricts the reliability and generalizability of research findings. Future studies with larger cohorts will incorporate aphasia subtype-based stratification to better capture potential differential responses across aphasia phenotypes. Furthermore, the absence of long-term follow-up in this investigation confines our observations to short-term therapeutic outcomes, thereby hindering a comprehensive understanding of treatment efficacy in sustained recovery processes. This methodological gap may obscure the longitudinal trajectory of therapeutic interventions.

Additionally, substantial heterogeneity exists within the PSA population regarding lesion topography, infarct volume, aphasia subtypes (e.g., Broca's aphasia, Wernicke's aphasia), and severity stratification (64). Such clinical variability complicates comparative effectiveness analyses across studies, as differential treatment responses among patients may substantially influence outcome interpretation. The inherent neurobiological diversity in this population necessitates cautious generalization of therapeutic outcomes. Perfusion imaging such as ASL was not included in the current protocol. Future studies should integrate cerebral blood flow measurements to better capture hemodynamic contributions to language recovery.

Lastly, although the pre-SMA also participates in motor control and planning, this protocol prioritizes language-related outcome measures to specifically evaluate speech network modulation. Including motor assessments such as the Fugl–Meyer or ARAT will be considered in subsequent studies to further disentangle motor- and language-specific contributions to recovery mechanisms.

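### The stated stratification has only one stratum, so allocation is in effect unstratified, and the stimulated hemisphere is neither balanced by design nor a term in the stated models

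*Protocol article*

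**What the plan says.** The Randomization section gives the ratio, "Participants will be randomly allocated in a 1:1 ratio to either the active iTBS or sham group", and then the stratification: "Randomization will be stratified by aphasia subtype (non-fluent only) to maintain balanced group allocation". Under Participants and recruitment, "only patients with non-fluent aphasia (as classified by the WAB) will be included". The Limitation section adds: "Future studies with larger cohorts will incorporate aphasia subtype-based stratification".

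The side of stimulation follows from the relative FA of the FAT, with a cut at 0.5 (Personalized stimulation target localization): "Participants with high FAT integrity receive stimulation over the ipsilesional pre-SMA, while those with disrupted FATs are stimulated over the contralesional pre-SMA". The Introduction gives the rationale, a model in which "functional recovery mechanisms are determined by the degree of structural reserve in the damaged hemisphere".

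On timing, the Blinding section has unblinded staff "perform randomization once individualized iTBS targets are determined". Table 1 ticks randomisation in the column "Screening and allocation", Day −7 to −1, and ticks the first MRI at Day 0, under the post-randomisation heading.

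On analysis, the behavioural, connectivity and FA models are each described with group and time (or phase) only. Lesion delineation and quantification separately says that lesion volume and the lesion–FAT overlap ratio are covariates.

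**The concern.** A stratification factor balances the arms only across its levels. Here eligibility has already reduced the factor to one level, so the sentence describes a safeguard that does nothing. A reader would credit the trial with a protection that it does not have.

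The design also contains a baseline factor with a much stronger claim to be balanced. FAT class determines which of two interventions a participant receives (ipsilesional or contralesional stimulation, real or sham), and the protocol's rationale ties it to how recovery proceeds. FAT FA is itself an analysed outcome. With 40 participants, an uneven split of FAT class between arms is a realistic event, and the stated models have no term for it. At stake are the precision of the AQ, connectivity and FA contrasts and the comparability of the arms in the trial that is actually run.

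**Working it through.** **1. Number of strata.** Eligible levels of the factor: 1 (non-fluent). Strata = 1, holding all 40 participants. This is the same as 1:1 allocation with no stratification. One could read the factor as subtypes within non-fluent aphasia, but no such levels are named and the Limitation section defers subtype stratification.

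**2. The plan's own figure.** The only stated number this point uses is the sample size: 16 / (1 − 0.20) = 20 per group, 40 in total. The dropout step reproduces.

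**3. Chance imbalance in stimulated hemisphere.** Inputs: N = 40 with 20 per arm (Sample size estimation), and K = the number with low FAT integrity, who are stimulated contralesionally. The article does not give K, so a range is assumed. With arms fixed at 20:20, the number X of these patients in the active arm is hypergeometric:

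P(X = x) = C(K, x) · C(40 − K, 20 − x) / C(40, 20)

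The gap between arms is |X − (K − X)| = |2X − K|.

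- K = 3: the largest possible gap is 3, so P(gap ≥ 4) = 0.
- K = 4: all four must fall in one arm. P = 2 · C(20, 4) / C(40, 4) = 2 × 4,845 / 91,390 = 0.106.
- K = 12: P(X ≤ 4) + P(X ≥ 8) = 0.301, that is, a split of 8:4 or worse.

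| K of 40 (assumed) | P(gap ≥ 4), arms 20:20 | P(gap ≥ 6), arms 20:20 | P(gap ≥ 4), unrestricted allocation |
|---|---|---|---|
| 3 | 0 | 0 | 0 |
| 4 | 0.106 | 0 | 0.125 |
| 8 | 0.235 | 0.044 | 0.289 |
| 12 | 0.301 | 0.082 | 0.388 |
| 16 | 0.333 | 0.105 | 0.454 |
| 20 | 0.343 | 0.113 | 0.503 |

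The last column uses a binomial (K, 0.5) and applies only if arm sizes are not held equal; for K = 4 it is 2 × 0.5⁴ = 0.125. The article does not describe how the sequence is generated, so the 20:20 columns are the ones to rely on.

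**4. What a gap does to the contrast.** A gap of g shifts the difference between arms in mean change by g/20 times the difference in mean change between the two FAT classes. An 8:4 split is 40% against 20%, so the shift is 4/20 = 0.2 of that difference. The documents give no figure for the between-class difference, so the shift cannot be put in AQ points.

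**5. With stratification.** Permuted blocks of 4 within each hemisphere stratum, taken for illustration only, hold the gap to at most 2 per stratum, so a gap of 4 or more cannot occur.

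**6. Is hemisphere available at allocation?** The Blinding section says yes, because targets are set first. Table 1 says no, because randomisation falls on Day −7 to −1 and the first MRI on Day 0. The document does not settle this.

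**The case against.** The strongest reply is that the one-level stratifier is a wording slip and that the rest is a suggestion rather than an error. Several parts of that reply stand.

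- **Tract damage is not ignored.** Lesion–FAT overlap is a planned covariate and measures damage to the same tract, so it may absorb part of an imbalance. But it is not the rFA class or the stimulated side, it does not balance the arms, and the model descriptions do not repeat it.
- **Pre-to-post analysis removes stable baseline differences.** Only a difference between FAT classes in change over time would matter.
- **Balanced allocation may mean equal arm sizes.** If the sequence is blocked, a single stratum can deliver that. A reader might infer that allocation must be simple randomisation, but the article does not say so. It supports only the statement that allocation is unstratified.
- **The rationale concerns mechanism.** A reader might infer that FAT class predicts how much patients recover. The Introduction links structural reserve to the mechanism of recovery, and the prognostic factors it names are age and aphasia severity.
- **K may be small.** If nearly everyone falls in one rFA class, imbalance is rare and stratification gains little.

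None of this rescues the stratification sentence, which contradicts the eligibility criteria and the Limitation section whatever K is.

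**Conclusion.** The point holds in two parts of different strength. The first needs no assumption: the claimed stratification has one stratum and balances no patient characteristic. The second is that stimulated hemisphere, the factor on which the intervention turns, is left to chance and is absent from the stated models. Its size depends on an unknown K: with 20:20 arms, the chance of a gap of 4 or more runs from 0% (K = 3) through 11% (K = 4), 24% (K = 8) and 30% (K = 12) to 34% (K = 20).

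A reader might infer that the treatment effect is confounded with FAT class. The documents do not support that. Imbalance arising by chance under randomisation does not bias the comparison or inflate the type I error; it costs precision and weakens the comparability of the arms. A reader might also take hemisphere as known at allocation. That rests on the Blinding section alone, and Table 1 says otherwise. The trial is not invalidated, but an empty safeguard is claimed where a useful one may be available cheaply.

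**What to change.** 1. Delete the claim of stratification by aphasia subtype.
2. Reconcile the Blinding section with Table 1 on whether randomisation comes before or after the baseline MRI and target determination.
3. If targets are determined before allocation, stratify by stimulated hemisphere (ipsilesional or contralesional), using two separately numbered, concealed envelope sequences.
4. In either case, add stimulated hemisphere as a term in the AQ, connectivity and FA models, alongside lesion volume and lesion–FAT overlap. It is a baseline factor defined in the same way in both arms, so it can be modelled even if it cannot be used at allocation or if some participants are already randomised.

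The cost is a second envelope sequence and one degree of freedom, with a small risk of an incomplete block in the rarer class. No targeting rule or treatment parameter changes. The benefit is small if nearly all participants fall in one rFA class.
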